**Results:**

Ethical approval for this study was given by the Clinical Research Committee of Andalusian Health Service, Spain (CI 1020-N-17), in June 2018. The community promoter has been identified, received an expert community-based palliative care course, and will start making contacts in the community and the palliative care teams involved in the research project.

**Conclusions:**

The results of this study will provide evidence of the benefit of the REDCUIDA protocol on the development and assessment of networks of compassionate communities at the end of life. It will provide information about clinical and emotional improvements, satisfaction, proxy burden, and health care resource consumption regarding patients in palliative care.

**Registered Report Identifier:**

RR1-10.2196/10515

## Introduction

### Palliative Care in the Community

Palliative care provides professional, scientific, and human responses to the needs of those living with advanced disease or facing the end of life, while also supporting their families [1]. Experts in this field are organized into multidisciplinary teams to provide a comprehensive care model to address suffering, symptom management, and other emotional, social, and spiritual aspects of the final stage of life, death itself, and the grief of relatives [2]. Palliative care is a type of care that best responds to the needs of these people and their families in such circumstances [3] and is internationally recognized as a right of citizens [4]. Palliative care can be provided across multiple settings. Studies indicate that, while aiming to be holistic, palliative care resources cannot possibly cover all patient and family needs [5]. Furthermore, differences in family structure mean that some patients might require more social and practical support than others. In these cases, mobilization of a person’s wider support networks can play a crucial role [6].

The main family caregiver is recognized as the person most involved in the patient’s care. This person, in Latin countries, usually is the contact with health and social care professionals and has to cope with the patient’s daily physical, social, and emotional needs [7]. Outside of the immediate family network, other support networks can assume other necessary tasks [6]. Evidence suggests that up to 7 different profiles have been identified of people who participate in the care of someone facing a terminal illness [8]. Mobilization of this wider network is the base of compassionate communities [9].

Kellehear’s theoretical framework of a compassionate community is gathering momentum internationally [10-12]. This new model of care operating in countries including the United Kingdom [13], Ireland [14], India [15], Canada [16], Australia [17,18], and Spain [19,20] brings together not only health and social professionals and primary caregivers but also the wider community (including extended family members, friends, neighbors, volunteers, and work colleagues) to support people and their families at the end of life. At a wider organizational level, the model of care may also include schools, universities, workplaces, companies, the arts community, social care and community development organizations, and policy makers [21]. It is intended that, through such a model of community intervention, there is an awakening and heightened activity of citizens regarding palliative and compassionate care [10-22]. Compassionate communities integrate and promote palliative care socially [23-25].

Health care organizations and policy makers are increasingly involved in the design, development, and evaluation of compassionate community models. It is recognized that they offer an opportunity to support the reconfiguration of health and social services, reduce costs, and facilitate models of integrated care [9]. The World Health Organization has included the development of compassionate communities based on awareness, training, and implementation of networks into their guide for the planning and implementation of palliative care services [26,27].

One of the largest and most successful models of compassionate communities in the world began in Seville, Spain. All with You [28] (a direct translation of the program’s Spanish name, *Todos Contigo*) is a social innovation program created by the New Health Foundation in 2014 [19]. It seeks to transform care for people with advanced chronic conditions that require palliative care by monitoring and optimizing health care and social services, providing support to families, mobilizing community-based assets, and promoting greater awareness of the challenges and opportunities associated with palliative care and the management of complex chronic conditions.

To our knowledge, no protocol or tool is available to assess systematically these types of intervention, so it remains difficult to compare them and to assess their real effect.

As a part of the All with You program, the REDCUIDA (short for *Redes de Cuidados*, or Network of Care) intervention protocol has been developed. This protocol will offer a systematic method to assess the quality of the community intervention and its effect on clinical well-being, patient and family satisfaction, and consumption of health system resources.

### Objective

The primary objective of this study is to evaluate the REDCUIDA intervention protocol for the creation and management of networks of care that cover the unmet needs of a person with advanced diseases or at the end of life.

The secondary objectives are to (1) identify the precise nature of a patient’s unmet needs by palliative care teams that can be addressed through mobilization of the community, (2) detect members of the support networks that can meet the patient’s identified needs and describe their fundamental characteristics (caregiver profiles), (3) analyze the influence of a community promoter’s interventions on the emergence and growth of support networks as the disease progresses, (4) assess whether the REDCUIDA intervention improves the patient’s quality of life and decreases the main caregiver’s burden, (5) establish whether this intervention reduces professionals’ workload and health and social resource consumption during end-of-life care, and (6) analyze the influence of the REDCUIDA intervention on the preference of the place of care and death.

### Hypothesis

We hypothesize that the use of the REDCUIDA protocol in a community intervention program allows for the expansion of care networks that can meet the needs and improve the quality of life of patients, increase family satisfaction, reduce the burden on main caregivers, improve the possibilities of care and death in the preferred place, and reduce the consumption of health care and social care resources during the end of life.

## Methods

### Trial Design

The study is a 2-year nonrandomized controlled trial using a 2-arm parallel group design conducted in the community. For the intervention group, we will combine the standard palliative care treatment with a community promoter’s intervention; the control group will benefit from standard palliative care.

Intervention and control group participants will be patients under the community palliative care team’s supervision living in 2 areas with and without community promoter intervention.

### Setting

The study will be developed in the community, in 2 different geographic areas in Seville, Spain. The main difference between them will be the presence of a community promoter as a part of a new city program called All with You [19].

### Eligibility Criteria

Inclusion criteria are patients living in Seville, with any advanced or terminal illness and receiving palliative care supervision, and having any of the following conditions: (1) total or serious dependence for basic and instrumental daily activities (Barthel Activities of Daily Living Index score <40; Lawton and Brody Instrumental Activities of Daily Living Scale score <3), (2) more than 40% of their needs not covered by the community, (3) a high score in loneliness on the Scale of Social Loneliness (ESTE) II (score >20 points), (4) having a person (family member, friend, neighbor, social worker, or other person) who acts as a communicator and principal person for support and is prepared and able to participate in the development of the network of care and share information with the community promoter, (5) having a main caregiver with an intense physical or emotional burden (scoring >56 on the Zarit Scale), and (6) accepting of the support and guidance by the community promoter with informed consent.

Exclusion criteria are patients who are in a very advanced terminal stage with life expectancy less than 1 week; those who do not have a high level of dependency and have their needs met by their family and other members of the community; and those who do not wish to participate.

### Recruitment Procedure

Potential participants will receive information from palliative care team members. Reasons for declining to participate will be recorded as not interested, too busy, don’t believe in it, and other.

Palliative care teams will arrange an appointment with the patient for the baseline assessment. This first appointment will take place in the patient’s home. At this appointment, written informed consent for participation in the study will be obtained from participants.

Patients assigned to the intervention group will be those living in the San Pablo-Santa Justa area, Seville (60,000 inhabitants), who accepted the community promoter intervention. Patients assigned to the control group will be those living in an area with no community promoter available.

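### Intervention patients must accept the community promoter and controls face no matching condition; the eligibility list does not level this and lets acceptance or a contact person stand in for need

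*Protocol article*

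**What the plan says.** The Recruitment Procedure section gives the two arms different entry rules. The intervention group is "those living in the San Pablo-Santa Justa area, Seville (60,000 inhabitants), who accepted the community promoter intervention". For the other arm it says: "Patients assigned to the control group will be those living in an area with no community promoter available". The same section takes written study consent at the baseline visit without limiting it to one arm, and the exclusions remove anyone unwilling to take part.

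The Eligibility Criteria section asks for patients "receiving palliative care supervision, and having any of the following conditions", followed by six items. Items 1, 2, 3 and 5 describe need: serious dependence, "more than 40% of their needs not covered by the community", high loneliness, and high caregiver burden. Item 4 is a contact "who acts as a communicator and principal person for support and is prepared and able to participate in the development of the network of care". Item 6 is "accepting of the support and guidance by the community promoter with informed consent". One exclusion limits the list: it removes "those who do not have a high level of dependency and have their needs met by their family and other members of the community".

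The Statistical Methods section compares the groups with a t test, Mann-Whitney or chi-square test. A linear regression is mentioned with the pre/post analysis of each group, and no covariate is named. The limitations section concedes possible selection bias because the trial is not randomized.

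**The concern.** An intervention-area resident who would join the study but declines the promoter belongs to neither arm. The same kind of person in the control area is enrolled and counted. The comparison is therefore accepters against a mixture of would-be accepters and would-be decliners.

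Willingness to let an outsider organise help plausibly bears on how large a network becomes, how many needs it covers and how satisfied the family is, and all three are measured. It is not among the variables listed in the article, and the recruitment text records only reasons for declining to participate. A later analysis could not adjust for it if it was never collected in controls.

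The eligibility wording adds a second problem. The primary objective concerns networks that cover unmet needs, yet two of the six alternative routes into the study say nothing about need.

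**Working it through.** **1. The entry rules side by side**

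- Intervention arm: lives in the intervention area, consents to the study, accepts the promoter.
- Control arm: lives in an area without a promoter, consents to the study.

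The difference is promoter acceptance.

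**2. Can criterion 6 restore balance?**

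- List read as any one of six (as written): a control qualifies through any of items 1 to 5, so item 6 does not bind controls.
- List read as all six: controls have no promoter to accept, so none could qualify.

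Neither reading gives a rule that works the same way in both areas.

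**3. Who can enter without meeting a need criterion?**

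Take a patient with no serious dependence, some uncovered needs but not above 40%, a loneliness score not above 20 and a Zarit score not above 56. Items 1, 2, 3 and 5 all fail. Item 4 or item 6 is enough for inclusion. The exclusion needs low dependency together with needs met; some needs are unmet, so it does not apply and the patient enters. A patient with low dependency and all needs met is excluded.

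**4. The plan's own group size**

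Sample Size Calculation: 700 × 0.65 = 455, and 455 × (1 − 0.30) = 318.5, which matches the stated 320. It is a count of available patients. No SD or baseline rate is given, so the size of any bias has to be illustrated on assumed values.

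**5. Illustration of the bias**

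Assumptions not in the documents: the areas are otherwise alike; the treatment has no effect; a share a of study-consenting eligible residents would accept the promoter; accepters and decliners differ by d SD; the test is two-sided (the article gives alpha 0.05 without sidedness).

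The overall mean is a × (accepter mean) + (1 − a) × (decliner mean), so accepters differ from it by

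bias = (1 − a) × d.

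With 320 per group the standard error is √(2/320) = 0.0791 SD. The chance of a significant result is Φ(bias/SE − 1.96) + Φ(−bias/SE − 1.96).

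For a = 0.7 and d = 0.2: bias = 0.30 × 0.2 = 0.06 SD, bias/SE = 0.76, rate = 11.8%.

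| Acceptance a | d = 0.2 | d = 0.3 | d = 0.5 |
|---|---|---|---|
| 0.9 | 5.7% | 6.7% | 9.7% |
| 0.7 | 11.8% | 20.7% | 47.5% |
| 0.5 | 24.4% | 47.5% | 88.5% |

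Sensitivity to group size: one year of the same headcount in an area of 60,000 gives 60,000 × 0.007 × 0.65 × 0.70 = 191. With 191 against 320, SE = √(1/191 + 1/320) = 0.0914, and the corresponding rates are 5.5% (a = 0.9, d = 0.2), 10.1% (a = 0.7, d = 0.2) and 78.1% (a = 0.5, d = 0.5).

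**The case against.** The design is openly nonrandomized and the article admits selection bias, so the reader is warned. A fuller analysis plan may add covariates. The eligibility list may also be loose drafting: item 6 mentions informed consent, which participants in general must give, and the sample size section speaks of patients failing to meet all the criteria. Both suggest that item 6 was not meant as a stand-alone route.

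The drafting point stands as an explanation, but it does not supply a usable rule, because requiring every item shuts out controls. The general caveat does not mention this particular filter, which can be avoided without randomizing. Covariates cannot replace a willingness measure that controls never gave.

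Several stronger readings are tempting and are not supported:

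- *Controls are unfiltered.* They consent to the study, and those unwilling to take part are excluded, so part of the willingness difference is screened in both arms.
- *A patient with no need of any kind can enter on item 4 or 6.* The exclusion bars anyone with neither high dependency nor unmet need.
- *Patients with nothing to gain dilute the effect by a calculable amount.* A highly dependent patient whose needs are all met can enter, but may still change on caregiver burden, satisfaction or resource use. A power loss cannot be worked out, because 320 is a headcount and no effect size in SD units is given.
- *The bias favours the intervention.* Accepters might be more open to help, or they might be lonelier and more burdened. The documents do not settle the direction.
- *The 30% in the sample size section is a refusal rate for the promoter.* It pools non-consent with ineligibility.

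**Conclusion.** The concern holds in this form: the arms differ by an avoidable acceptance condition on top of study consent, the eligibility list does not remove that difference under either reading, and nothing else in the article handles it. That conclusion rests on the text alone.

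The size is conditional. Over the assumed grid, the chance of a falsely significant difference at 320 per group goes from barely above nominal (5.7%) to 88.5%, with 11.8% at a moderate setting, more than twice the nominal 5%. The bias may equally hide a real benefit. No single cell of the table should be read as an estimate for this trial.

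The eligibility wording is a related but smaller matter. It admits patients who have some need but fall below all four need thresholds, and it should be reconciled with the stated objective.

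**What to change.** Use one entry rule in both areas, by either route.

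1. **Willingness question.** At control consent, ask whether the patient and family would accept a community promoter if one were available. Record the answer, and compare intervention accepters with control-area would-be accepters. Cost: one question and slightly fewer controls. The answer is hypothetical, so the match is closer but not exact.
2. **Analysis by area.** Enrol all consenting eligible residents in both areas, follow them alike, and compare by area of residence whether or not the promoter was accepted. Cost: decliners dilute the effect somewhat, and the result describes offering the promoter rather than receiving one.

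Under either route, rewrite the inclusion list so that items 4 and 6 are not routes to entry on their own, and word item 6 so that a control can meet it. If the authors also want to leave out highly dependent patients whose needs are already covered, they must say so separately, since this rewording would still admit them through item 1. The change should be made before controls are enrolled: a willingness answer not taken at consent may not be recoverable later in patients near the end of life.

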### Intervention

We will deliver the REDCUIDA intervention over the course of 7 weeks (Figure 1). Different interventions will take place each week during a face-to-face meeting between the community promoter and the person living with advanced illness, or their families, or both.

We will conduct an initial (V0) assessment of the sociodemographic data of the beneficiary and his or her needs. This first step aims to detect the degree of care and support networks that could be mobilized during the progression of the disease. At this point, the community promoter will complete the beneficiary’s referral sheet (Multimedia Appendix 1) and the requirements sheet (Multimedia Appendix 2 [29]). If more detailed information will be needed, a face-to-face meeting will be held with the health professional involved.

Following V0, we will determine the needs of care networks and interventions. Then, we will arrange a meeting among the beneficiary and his or her family, health care professionals, and the community promoter to inform all of them about creating and managing a specific caring network within their community (V1). This first visit will be used to understand the starting point as a baseline analysis for the activities ahead.

During the subsequent interventions, we will conduct several assessments (Table 1) based on the following scales. We will use the Barthel Index [29], in the original or a validated Spanish version [30], to identify needs related to basic daily living activities. This assessment can be self-administered, evaluated with direct observation, or completed by the patient or caregivers (Multimedia Appendix 2). We will use Lawton and Brody’s original scale [31] to identify needs for instrumental daily living activities. This assessment can be self-administered, directly observed, or completed by the patient or caregivers (Multimedia Appendix 2).

**Figure 1 figure1:**
[figure not shown]
Action procedures for the REDCUIDA protocol.

**Table 1 table1:** REDCUIDA protocol for applying assessments to the beneficiary and the networks of care.

Assessment	Evaluation step							
	V0	V1	V2	V3	V4	V5	V6	V7
Inclusion and referral sheet	Yes	—	—	—	—	—	—	—
Networks of care	Yes	Yes	Yes	Yes	Yes	Yes	Yes	—
Barthel Index	Yes	Yes	Yes	Yes	Yes	Yes	Yes	—
Lawton and Brody scale	Yes	Yes	Yes	Yes	Yes	Yes	Yes	—
Loneliness scale	Yes	—	—	—	—	—	Yes	—
Zarit Scale	Yes	—	—	—	—	—	Yes	—
EQ-5D-3L^a^	—	—	—	—	—	—	Yes	—
Family and network of care satisfaction	—	—	—	—	—	—	—	Yes

^a^EQ-5D-3L: 3-level EuroQol 5 dimensions questionnaire.

We have adapted Abel and colleagues’ circles of care (Multimedia Appendix 3) [6], which can be self-administered or assessed via a direct interview with the patient or their caregivers. We will detect social solitude using the expanded ESTE II Scale [32] adapted from De Jong Gierveld and Van Tilburg [33], which must be administered directly to the patient or by the caregiver (Multimedia Appendix 4). We will use the 3-level EuroQol 5 dimensions questionnaire (EQ-5D-3L) [34] to asses quality of life. This descriptive system contains 5 dimensions of health (mobility, personal care, daily activities, pain and discomfort, and anxiety and depression), and each has 3 levels of severity (no problems, some problems or moderate problems, and serious problems). This assessment is self-administered or completed directly by the patient (Multimedia Appendix 5). We will use the Zarit Scale [35,36] adapted into Spanish [37] to assess the variable burden of the caregiver in the provision of care to chronically ill patients, which is administered by directly interviewing the caregiver (Multimedia Appendix 6). The Satisfaction Scale, adapted from Villavicencio et al [38] and Molina et al [39] (Multimedia Appendix 7), will be conducted by an external professional by phone on completion of the interventions.

During the intervention processes and the creation of networks of care, the community promoter will follow a series of activities based on Horsfall and colleagues’ method for the creation of ecosystems of care around people at the end of life [40].

At the end of the interventions, a final evaluation (V7) will be conducted to reevaluate the needs coverage by the network and to evaluate family and caregivers’ satisfaction. This phone questionnaire will be administered by an independent professional to avoid information bias.

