### Variables

The variables we will use for the descriptive study on the REDCUIDA protocol are the following: for patients’ clinical and sociodemographic data: age, sex, and diagnosis; for families’ sociodemographic data: age, sex, and relationship to the patient; for network of care profiles: relationship to the patient, age, and sex; number of needs according to Barthel Index and the Lawton and Brody scale; number of members of the care network; number of needs covered by the network; quality of life according to the quality of life scale EQ-5D-3L; degree of loneliness according to ESTE II Scale; burden of the principal caregiver according to the Zarit Scale; satisfaction regarding the care network according to the Satisfaction Scale; and place of death.

For community promoter activity data, we will determine the number of interventions performed at home and number of interventions carried out in the community (eg, district, neighborhood, city, community of neighbors).

To assess health care system resources, we will determine the number of hospital admissions in the last month; days of hospital stays in the last month; number of emergency visits in the last month; number of visits of the palliative care team to the home; number of visits of the palliative care team to a hospital; and number of telephone calls made by the palliative care team.

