### Statistical Methods

We will carry out an initial descriptive analysis of variables related to patients’ needs and the profiles of people involved in the social network by degree of kinship.

We will analyze pre- and postintervention data for each group. These will include measures of central tendency (mean), confidence intervals for the 95% average, contingency tables (frequencies), and a linear regression.

To compare the groups, we will compare means. For continuous variables, we will use Student *t* test to compare independent samples with normal distribution and Mann-Whitney *U* test for nonnormal distributions. For discrete variables, we will use Mann-Whitney *U* test. For dichotomous variables (comparison of proportions), we will use Pearson chi-square test. All tests will be carried out with a significance level alpha=.05.

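### EQ-5D-3L, the only quality-of-life measure, has no baseline in Table 1, and preferred place of care or death is not a listed variable, so the quality-of-life half of objective 4 and objective 6 are poorly supported

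*Protocol article*

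**What the plan says.** **Quality of life.** Secondary objective 4 (Objective) is to "assess whether the REDCUIDA intervention improves the patient’s quality of life and decreases the main caregiver’s burden", and the Hypothesis also expects better quality of life. The Intervention section, in the text below Table 1, says "We will use the 3-level EuroQol 5 dimensions questionnaire (EQ-5D-3L) [34] to asses quality of life". The Variables section names the same single measure: "quality of life according to the quality of life scale EQ-5D-3L". In Table 1 the EQ-5D-3L row has all eight cells. Seven are dashes and the only Yes is at V6. The row for the other half of the same objective reads "Zarit Scale Yes — — — — — Yes", so burden has a V0 and a V6 value. Loneliness follows the same pattern, and Barthel and Lawton and Brody are taken at every step from V0 to V6.

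On analysis, Statistical Methods says "We will analyze pre- and postintervention data for each group", and the Abstract states that results will rest on a baseline and a final assessment after 7 weeks. Groups are compared by simple tests of means, ranks or proportions.

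**Place.** Secondary objective 6 is to "analyze the influence of the REDCUIDA intervention on the preference of the place of care and death". The Hypothesis expects the intervention to "improve the possibilities of care and death in the preferred place". The Variables section lists place of death and no other item on place.

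**The concern.** An objective about improvement needs a starting value or groups that are comparable at the start. This plan has neither for quality of life. Under Recruitment Procedure, the intervention group lives in one named area and has accepted the promoter, and the control group lives in an area without one. The Possible Limitations section concedes that selection bias is possible. With EQ-5D-3L taken once, at the end, a difference between the areas that existed before the intervention could be reported as an effect, or could hide one, and the data would not show which.

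For place, the objective and the hypothesis both turn on what the patient prefers. If the preference is not recorded, where a patient died cannot be classed as matching it or not.

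**Working it through.** **1. Schedule against objective.**

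| Outcome | Objective | V0 | V6 | Change can be formed |
|---|---|---|---|---|
| Caregiver burden (Zarit) | 4 | yes | yes | yes |
| Loneliness (ESTE II) | – | yes | yes | yes |
| Quality of life (EQ-5D-3L) | 4 | no | yes | no |

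V1, which the Intervention section also describes as a baseline point, has no EQ-5D-3L either. Nothing else in the article schedules an earlier one.

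**2. The number per group.** The stated 320 reproduces as a count of available patients: 700 × 0.65 = 455, and 455 × (1 − 0.30) = 318.5. It is not derived from an EQ-5D difference, and the article gives no SD, area gap or correlation for EQ-5D-3L. Those below are assumptions.

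**3. What an unseen baseline gap does.** Assume no true effect, 320 analysed per group, a two-sided test at 0.05 (the article does not state sidedness) and a comparison of V6 values alone. Let the baseline gap be b SD, of which a fraction ρ (the baseline-to-V6 correlation) is still present at V6.

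- Bias at V6: d = ρ × b
- Standard error: SE = √(2/320) = 0.0791 SD
- Probability of a significant result: 1 − Φ(1.96 − d/SE) + Φ(−1.96 − d/SE)

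| b (SD) | ρ = 0.5 | ρ = 0.7 |
|---|---|---|
| 0.1 | 0.097 | 0.144 |
| 0.2 | 0.244 | 0.425 |
| 0.3 | 0.475 | 0.757 |

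For b = 0.2 and ρ = 0.5: d = 0.10, d/SE = 1.26, probability 0.244. If the whole 0.2 SD gap is still there at V6: d/SE = 0.20/0.0791 = 2.53, probability 0.716. If only 160 per group reach V6 with that full gap: SE = √(2/160) = 0.1118, d/SE = 1.79, probability about 0.43.

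**4. What a V0 value would remove.** If the gap shrinks to ρ × b by V6, adjustment with slope ρ removes it. If it persists in full and the correlation is 0.5, adjustment removes 0.5 × 0.2 = 0.10 SD and leaves 0.10 SD. The residual variance factor is 1 − 0.5² = 0.75, so SE = 0.0791 × √0.75 = 0.0685, d/SE = 1.46, and the false-positive rate is still about 31%, against 72% without adjustment.

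**5. Place.**

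| Needed for objective 6 and the Hypothesis | In the Variables section |
|---|---|
| Preferred place of care | no |
| Preferred place of death | no |
| Actual place of care | no |
| Actual place of death | yes |

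One of four items is listed. Neither a change in preference nor agreement with preference can be computed from it.

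**The case against.** A reader might infer that objectives 4 and 6 cannot be answered at all and that imbalance cannot be corrected. The article does not support either inference in full.

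- Burden, half of objective 4, has a baseline and is unaffected.
- A V6 comparison of EQ-5D-3L between areas can be computed. It is weak evidence, but it is possible.
- Barthel, Lawton and Brody, loneliness and Zarit are taken at V0; age, sex and diagnosis are recorded; and a linear regression is mentioned. Mobility, personal care and daily activities overlap with Barthel and Lawton content, so partial adjustment is available. Pain and discomfort, and anxiety and depression, are not covered by those two scales, and the outcome's own baseline is missing.
- The pre/post sentence in Statistical Methods is general and need not promise a change score for every variable; satisfaction too is taken once. The firmer conflict is between Table 1 and objective 4, which speaks of improvement.
- The appendix forms are not shown and might contain a question on preferred place. Even so, no listed variable uses one.
- These are secondary objectives, and the article already admits possible selection bias.

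These points limit how strongly the concern can be put. They do not supply the missing EQ-5D-3L baseline or the missing place variables.

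**Conclusion.** The point stands in limited form. For quality of life, the schedule gives no within-patient change and leaves a V6 difference confounded with any earlier EQ-5D difference between the areas. For place, the listed variables do not reach the preference that objective 6 and the Hypothesis name.

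Both conclusions come from setting the article's sections side by side and need no assumed figure. The false-positive rates only illustrate the stakes. The 72% figure should not be quoted alone: it needs a gap of 0.2 SD, fully present at V6, with all 320 per group analysed, and the article states no such gap. With partial carry-over (0.5–0.7) the same gap gives 24–43%, and a gap of 0.1 SD gives 10–14%.

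Nor should a reader infer that a V0 measurement would settle the matter. It reduces confounding without removing it, and it does nothing about patients who die before V6.

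**What to change.** **Quality of life.** In Table 1, add EQ-5D-3L at V0, in both areas. In Statistical Methods, state that V6 EQ-5D-3L is compared between groups with adjustment for its V0 value, alongside the other V0 scores. The cost is five questions at the baseline home appointment that Recruitment Procedure already provides for, plus one change to Table 1. It has to be in place before patients pass V0, because a missed baseline cannot be recovered. The report should say that residual confounding and deaths before V6 remain.

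**Place.** Add to Variables the preferred place of care and preferred place of death, recorded at V0, and again at V6 if objective 6 means a change in preference. Add actual place of care. Analyse agreement with preference for place of care in all patients, and for place of death among those who die. The cost is a few items on existing forms.

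If these items cannot be collected, reword objectives 4 and 6 and the Hypothesis to match what is measured: final quality of life by area, and actual place of death.
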